## Abstract

**Background:** Idiopathic normal pressure hydrocephalus (iNPH) is a progressive neurological disorder characterized by cognitive decline, gait disturbances, and urinary incontinence. Surgical interventions such as ventriculoperitoneal shunt (VPS) and endoscopic third ventriculostomy (ETV) are the primary treatment options. While VPS is the standard of care, ETV offers a minimally invasive alternative with potentially fewer complications. However, comparative evidence regarding their impact on cognitive, motor, and structural outcomes remains limited. This study, titled ENVENTOR-iNPH (endoscopic ventriculostomy versus shunt on neuropsychological and motor performance in patients with iNPH), aims to address this gap through a rigorously designed comparative protocol. **Methods:** This protocol is designed as a multicenter, randomized, controlled trial (ENVENTOR-iNPH) to compare the effects of ETV and VPS in patients diagnosed with iNPH. The study will enroll 100 patients aged 60 years or older, randomly assigned to undergo ETV (n = 50) or VPS (n = 50). Preoperative and postoperative evaluations will include comprehensive cognitive and motor assessments, standardized quality-of-life instruments, and advanced neuroimaging techniques such as MRI with flowmetry and diffusion tensor imaging (DTI). Functional outcomes will also be evaluated using navigated transcranial magnetic stimulation (nTMS) and wearable motion analysis systems. The objective of this study is to compare the efficacy and safety of ETV versus VPS in restoring cognitive and motor performance in patients with iNPH. **Results:** Primary outcomes include cognitive and motor function improvements. Secondary endpoints are surgical complications, hospital stay duration, and changes in quality of life. Neuroimaging will assess changes in white matter integrity and cerebrospinal fluid dynamics, while nTMS will provide insights into neuroplasticity and motor pathway recovery. ETV is hypothesized to demonstrate clinical outcomes comparable or superior to VPS, particularly in terms of complication reduction and hospital recovery metrics. **Conclusions:** The ENVENTOR-iNPH protocol establishes the framework for a comprehensive, multicenter study comparing ETV and VPS in iNPH patients. The findings from this initial study will inform the design of larger-scale multicenter trials, guide clinical decision making, and potentially position ETV as a preferred treatment option for eligible patients.

## 1. Introduction

Idiopathic normal pressure hydrocephalus (iNPH) is a chronic neurodegenerative disorder that primarily affects older adults. It is characterized by Hakim’s triad of symptoms: cognitive decline, gait disturbances, and urinary incontinence [1,2]. Unlike other forms of hydrocephalus, iNPH occurs without an increase in intracranial pressure (ICP), yet it leads to progressive ventricular dilation. The exact pathophysiology remains unclear, but it is believed to involve impaired cerebrospinal fluid (CSF) absorption, resulting in ventricular expansion and compression of periventricular white matter tracts [1,2,3]. This compression disrupts the neural pathways responsible for cognitive, motor, and urinary control, thereby explaining the hallmark symptoms. Given the clinical overlap with Alzheimer’s and Parkinson’s diseases, iNPH is frequently misdiagnosed, delaying timely intervention.

Surgical treatment is the most effective approach for managing iNPH, with ventriculoperitoneal shunt (VPS) and endoscopic third ventriculostomy (ETV) being the two most widely used techniques [4,5,6]. VPS involves diverting excess CSF from the ventricles to the peritoneal cavity using an implanted device, thereby relieving ventricular pressure. While effective, VPS carries risks of infection, device malfunction, and over-drainage, often requiring shunt revisions [7]. By contrast, ETV creates a direct flow path for CSF from the third ventricle into the subarachnoid space, bypassing the need for an implantable device. ETV reduces the risk of infection and device-related complications but is dependent on favorable patient anatomy and surgical precision [8].

Both procedures are effective in alleviating the symptoms of iNPH, with gait improvement often seen as the earliest and most prominent benefit [9]. However, the impact on cognitive recovery is less consistent, with prior studies suggesting that early surgical intervention leads to better cognitive outcomes. While previous research has demonstrated the efficacy of ETV and VPS independently, direct comparative studies are limited, and the relative long-term effectiveness of these techniques remains underexplored.

To address this gap, we have developed the ENVENTOR-iNPH (endoscopic ventriculostomy versus shunt on neuropsychological and motor performance in patients with iNPH) study protocol. This acronym reflects the central focus of the study, as also emphasized typographically in the manuscript title, where ENVENTOR-iNPH is distinguished to signal its importance as the study protocol name.

This study aims to provide robust evidence on the comparative cognitive, motor, and structural outcomes of ETV versus VPS using advanced neuroimaging, diffusion tensor imaging (DTI), and navigated transcranial magnetic stimulation (nTMS). By leveraging these tools, this study will offer new insights into the mechanisms of recovery and inform clinical guidelines for iNPH treatment. Although this initial protocol excludes patients with significant neurological comorbidities to maintain internal validity, we acknowledge this may limit generalizability. Future phases of the ENVENTOR-iNPH project will aim to include stratified cohorts with mild or early-stage comorbid conditions and potentially utilize biomarker-supported diagnoses to enhance translational relevance.

## 2. Materials and Methods

This study is structured as a randomized, controlled, multicenter clinical trial designed to compare the effects of ETV and VPS on the cognitive, motor, and structural outcomes of patients with iNPH. To ensure appropriate patient allocation between the ETV and VPS arms, standardized clinical and radiological criteria have been established. These include a positive response to the tap test (TT), the presence of gait disturbance, mild-to-moderate cognitive impairment, and radiological findings such as an Evans index > 0.3, callosal angle < 90°, and DESH. MRI with flowmetry will be used to assess anatomical suitability for ETV, particularly evaluating the configuration of the third ventricular floor and patency of basal cisterns. These uniform criteria will be used across all participating centers to ensure methodological consistency in this multicenter trial, which is aligned with the recently proposed six-step diagnostic and therapeutic algorithm endorsed by the Italian Society of Neurosurgery (SINCH) for the management of iNPH [10]. The trial will span a period of 36 months and involve multiple healthcare centers, ensuring a diverse and representative patient population to enhance the generalizability of the findings. The study protocol is named ENVENTOR-iNPH (endoscopic ventriculostomy versus shunt on neuropsychological and motor performance in patients with iNPH). A total of 100 patients diagnosed with iNPH will be enrolled and randomly assigned in a 1:1 ratio to undergo either ETV or VPS. Randomization will be performed using a computer-generated algorithm, ensuring allocation concealment and reducing the risk of selection bias. Eligibility criteria require participants to be 60 years or older with a confirmed diagnosis of iNPH. This diagnosis must be established through a combination of clinical neurological assessment, invasive diagnostic testing, and neuroimaging criteria. Invasive tests include the TT, which evaluates clinical improvement following CSF removal, and the LiquoGuard test, a continuous CSF monitoring and drainage procedure that provides detailed intracranial pressure and flow measurements. Neuroimaging will play a critical role in diagnosis and treatment planning, utilizing MRI and DTI to assess ventricular enlargement, periventricular white matter changes, and CSF flow dynamics. MRI with flowmetry will measure the velocity and dynamics of CSF circulation, aiding in confirming the diagnosis and determining the anatomical suitability for ETV. Patients will also undergo computed tomography (CT) imaging as part of the preoperative assessment to evaluate ventricular anatomy, assess for calcifications, and exclude contraindications such as significant basal cistern obstructions or intracranial lesions. Neuroimaging will also assess the presence of DESH (disproportionately enlarged subarachnoid space hydrocephalus), defined by widened Sylvian fissures, narrowed high-convexity sulci, and ventriculomegaly. Together, these diagnostic tools will provide a comprehensive evaluation of the patient’s condition, ensuring accurate diagnosis and optimal patient selection for the study. Exclusion criteria include the presence of comorbid neurological conditions, such as Alzheimer’s disease or Parkinson’s disease, which may confound outcome measurements, as well as anatomical variations (e.g., severely narrowed third ventricle floor or basal cistern scarring) that would render ETV technically unfeasible. Additionally, patients unable to provide written informed consent or who exhibit contraindications to invasive diagnostic tests will be excluded from participation. This rigorous approach to patient selection, encompassing both advanced neuroradiological imaging and invasive diagnostic testing, ensures a homogenous study population and enhances the reliability and validity of the trial’s outcomes.

### 2.1. Preoperative Evaluation

Preoperative evaluation is critical for establishing a detailed baseline of each patient’s neurological, cognitive, motor, and personality functions. It combines clinical assessments, advanced neuroimaging, and specialized tests to confirm the diagnosis and plan the surgical approach (Figure 1). All neuropsychological assessments, including WAIS-IV, RBMT-3, Raven’s matrices, and MMPI-2, will be administered preoperatively and repeated at each follow-up to allow longitudinal comparison. Motor assessments, including the Timed Up and Go (TUG) Test, Baiobit wearable sensor gait analysis, and the iNPH grading scale, will also be conducted both preoperatively and at each postoperative timepoint.

### 2.2. Neurological Examination and Scoring Systems

A detailed neurological examination will assess motor, cognitive, and sensory functions, with a particular focus on hallmark symptoms of iNPH, such as gait disturbances and reflex abnormalities. Objective tools include the following:Motor test: Timed Up and Go (TUG) Test, 6 min walk through the Baiobit system, a wearable inertial measurement unit (IMU) to measure precise balance, mobility, and fall risk [4].iNPH grading scale (iNPHGS): a validated tool to quantify the severity of gait, cognitive, and urinary symptoms, ranging from 0 (no symptoms) to 4 (severe impairment) [11].Kiefer score: integrates functional symptom severity with radiological findings, including ventricular enlargement and disproportionate subarachnoid spaces measured using the Evans index [12].

### 2.3. Neuropsychological Assessment

A series of standardized neuropsychological tests will evaluate the cognitive domains commonly affected in iNPH, providing critical data on intellectual, memory, and personality functioning:Raven’s progressive matrices to measure non-verbal intelligence and assess fluid reasoning and problem-solving abilities independent of cultural or educational background 4.Rivermead Behavioural Memory Test—Third Edition (RBMT-3), a memory test with ecological validity designed to predict memory deficits in real-life scenarios and monitor changes over time [12].WAIS-IV (Wechsler Adult Intelligence Scale—Fourth Edition) to provide a comprehensive evaluation of cognitive abilities, including general intellectual functioning, working memory, fluid intelligence, and processing speed [4,12].Minnesota Multiphasic Personality Inventory—2 (MMPI-2) to assess personality traits and emotional disorders, offering insights into psychological factors that may influence postoperative recovery [11].

In addition to these instruments, the Mini-Mental State Examination (MMSE) will be used to provide a rapid, global assessment of cognitive function. To evaluate balance and fall risk, the Berg Balance Scale (BBS) will be administered, and the Modified Rankin Scale (mRS) will be employed to assess overall functional independence and the degree of disability.

### 2.4. Neuroimaging

Advanced imaging protocols are critical for confirming the diagnosis and guiding surgical planning. The imaging protocol included the following:MRI with flowmetry, which evaluates CSF flow dynamics and identifies ventricular enlargement and disproportionate subarachnoid spaces. This imaging technique is particularly useful for determining anatomical suitability for ETV [4,11].Diffusion tensor imaging (DTI) to assess the integrity of periventricular white matter tracts and identify the structural changes associated with ventricular compression and potential recovery [12].CT scans, complementing MRI by evaluating calcifications, bone structures, and basal cistern anatomy, which are important for surgical feasibility [11].

### 2.5. Neuroinvasive Diagnostic Tests

Invasive tests will be used to confirm the diagnosis of iNPH:Tap test (TT), which involves removing a large volume of CSF to observe symptom improvement in gait, cognition, or urinary function, offering strong predictive value for surgical success 4.LiquoGuard Test, which provides continuous CSF drainage and intracranial pressure monitoring, delivering detailed data on CSF dynamics to validate the diagnosis and refine treatment plans [12].

### 2.6. Neurofunctional Evaluation

nTMS will be employed to assess cortical excitability and motor pathway integrity. This non-invasive technique uses magnetic fields to stimulate motor cortical regions, allowing for the mapping of motor pathways and the recording of motor evoked potentials (MEPs). nTMS will establish a baseline for corticospinal tract functionality, which will be critical for tracking postoperative motor recovery and neuroplasticity [12].

### 2.7. Surgical Procedures

Patients will be randomly assigned to undergo either ETV or VPS. Both procedures will be conducted by experienced neurosurgeons at the participating centers using standardized techniques to ensure consistency and safety.

### 2.8. VPS Surgery

The VPS procedure involves the placement of a catheter in the lateral ventricle to drain excess CSF into the peritoneal cavity, where it is reabsorbed. A programmable valve, chosen based on the surgeon’s clinical judgment, will regulate the flow of CSF. This approach allows for adjustments in drainage settings postoperatively to optimize patient outcomes and reduce complications such as over-drainage [12].

The surgical technique will follow the standardized steps, including positioning patients in the supine position, preoperative prophylactic antibiotics, placement of a ventricular catheter under neuronavigation, connection to a programmable valve, and distal catheter tunneling into the peritoneal cavity. Postoperative valve settings will be tailored individually, and infection control protocols will be uniformly applied across centers.

### 2.9. ETV Surgery

ETV is a minimally invasive procedure in which a small perforation is made in the floor of the third ventricle, creating a new pathway for CSF flow into the basal cisterns. ETV will be performed with the patient in the supine position using a rigid endoscope. After identifying anatomical landmarks, a perforation will be made in the third ventricular floor anterior to the mammillary bodies. Fenestration patency will be confirmed visually and with irrigation. Neuronavigation and intraoperative monitoring will assist in avoiding vascular injury and ensuring procedural safety [11].

### 2.10. Postoperative Evaluation

The postoperative follow-up protocol is designed to evaluate recovery and assess the efficacy of the surgical interventions. Follow-ups will occur at 1 week, 3 months, 6 months, and 12 months after surgery. During these evaluations, cognitive and motor assessments will be repeated, and imaging studies will track the structural changes in white matter and ventricular size. At the follow-up times, patients will undergo repeated neuropsychological and motor performance evaluations using the same tools administered preoperatively. This will enable a direct comparison of cognitive and motor recovery over time [4,12]. MRI with flowmetry and DTI will be performed during each follow-up to monitor changes in ventricular size, CSF flow, and white matter integrity. These imaging modalities provide critical insights into the structural effects of ETV and VPS on the brain [11,12]. At the same follow-up, nTMS will assess postoperative changes in corticospinal excitability and motor pathway recovery. Changes in MEPs will serve as objective indicators of neuroplasticity and functional improvement. Additionally, repetitive TMS (rTMS) may be explored as a therapeutic tool to further enhance motor recovery [12]. This integrated approach ensures a thorough evaluation of the effects of ETV and VPS on iNPH patients, providing a robust dataset to inform clinical decision making and improve treatment outcomes.

Quality of life will also be systematically assessed using the SF-36 Health Survey, a validated instrument capturing both physical and mental health domains from the patient’s perspective. This tool will be administered preoperatively and at each follow-up interval to longitudinally evaluate patient-reported outcomes.

### 2.11. Statistical Analysis

All statistical analyses will be conducted using IBM SPSS Statistics, version 30.0.0, and R, version 4.5.0. The threshold for statistical significance will be set at α = 0.05. Two-tailed tests will be used unless a specific directional hypothesis is stated (e.g., the anticipated superiority of ETV over VPS), in which case one-tailed tests will be applied.

Continuous variables will first be tested for normality using the Kolmogorov–Smirnov test, and for homogeneity of variance using Levene’s test. If assumptions of normality and homoscedasticity are met, parametric tests such as the independent-samples *t*-test will be used. For repeated measures data, linear mixed-effects models will be applied instead of a traditional ANOVA to account for intra-subject variability and missing data points. If assumptions are violated, appropriate non-parametric alternatives (e.g., Mann–Whitney U test, Wilcoxon signed-rank test) will be applied.

To control Type I errors in multiple comparisons, a Bonferroni correction will be applied where appropriate. In addition to *p*-values, effect sizes (e.g., Cohen’s d for *t*-tests, η^2^ or partial η^2^ for ANOVA) will be reported to quantify the magnitude of observed effects.

For the analysis of longitudinal data, mixed-effects models will be used to account for intra-subject variability across follow-up points. These models will include fixed effects for time and the treatment group, as well as random intercepts to capture individual-level variability.

An a priori power analysis was performed assuming an effect size of Cohen’s d = 0.5, power (1 − β) of 0.80, and α = 0.05 (two-tailed). The estimated required sample size was 51 participants per group. This effect size was selected as a conservative estimate based on previously published studies evaluating pre- and postoperative cognitive and motor changes in patients with iNPH. Nonetheless, we recognize that this estimate may be optimistic. If the true effect is smaller, a larger sample size would be needed to retain adequate statistical power. This limitation is acknowledged, and future extensions of the study may involve adaptive or sequential design strategies to account for observed variability.

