The primary outcome will be the change in cognitive and motor performance over time. Cognitive functions will be evaluated using neuropsychological tests, focusing on memory, attention, executive function, and language. All cognitive assessments will be conducted both preoperatively and at each postoperative follow-up interval, as stated in the protocol. Motor outcomes will be assessed through gait analysis and coordination tests. All motor assessments will likewise be performed preoperatively and postoperatively using standardized tools including the Timed Up and Go (TUG) Test, the Baiobit wearable system, and the iNPH grading scale. The preliminary expectations are that patients in both the ETV and VPS groups will experience significant improvements in gait, as gait disturbance is typically the first symptom to improve following iNPH surgery. However, the degree of cognitive improvement may differ between the two groups, as prior evidence suggests that early intervention and reduced white matter compression may promote better cognitive recovery. By comparing cognitive trajectories in the ETV and VPS groups, this study aims to determine whether ETV has comparable or superior cognitive benefits relative to VPS. Structural changes in the brain will be analyzed using diffusion tensor imaging (DTI) and magnetic resonance imaging (MRI) with flowmetry. DTI will track changes in white matter integrity over the 12-month follow-up period. Since periventricular white matter is particularly vulnerable in iNPH, changes in the integrity of white matter tracts, such as the corticospinal tract, will be examined. The integrity of these tracts is essential for motor coordination and cognitive functions. Tractography will be used to visualize white matter pathways before and after surgery, providing insight into how ETV and VPS differentially affect white matter recovery. Neurophysiological changes will be measured using navigated transcranial magnetic stimulation (nTMS). This technique will allow researchers to assess motor cortical excitability and map changes in corticospinal tract connectivity. Motor evoked potentials (MEPs) will be recorded before surgery and at all follow-up intervals. An increase in MEP amplitude after surgery would suggest improved cortical excitability and the potential recovery of motor function. Differences in MEP amplitudes between the ETV and VPS groups may offer additional evidence regarding which procedure promotes superior motor recovery. Secondary outcomes will include the rate of complications, intensive care unit (ICU) stay, and patient-reported quality of life. Patients in the VPS group are expected to have a higher incidence of device-related complications, such as infection, shunt malfunction, and over-drainage, compared to the ETV group, which does not require the implantation of a foreign device. ICU stay and hospital length of stay will be compared between the two groups, with the hypothesis that ETV patients will have shorter stays due to the less invasive nature of the procedure. Quality-of-life measures will be obtained from patient self-reports, providing insight into the broader impact of surgery on daily living and well-being.

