ETV has emerged as a promising alternative to VPS. This minimally invasive procedure involves the creation of a fenestration in the floor of the third ventricle, allowing CSF to bypass any obstruction and flow into the subarachnoid space [8,9]. Unlike VPS, ETV does not require the implantation of a foreign device, which significantly reduces the risk of infection and eliminates the need for lifelong device maintenance. Several studies have reported that ETV has a lower complication rate than VPS, with fewer incidences of infection, over-drainage, and mechanical failure [19]. However, ETV has its own limitations. Its success depends on the anatomical configuration of the patient’s third ventricle and basal cisterns, as well as the technical precision of the neurosurgical procedure [20]. In cases where the third ventricle anatomy is not suitable for fenestration, ETV may be ineffective, leading to treatment failure and the need for secondary surgical interventions. Moreover, ETV may not be appropriate for all patients with iNPH, especially those with anatomical variants or those with impaired compliance of the basal cisterns [21,22]. Despite these limitations, ETV has been associated with a lower rate of long-term complications and fewer hospital readmissions compared to VPS.

This trial, formally titled ENVENTOR-iNPH (endoscopic ventriculostomy versus shunt on neuropsychological and motor performance in patients with iNPH), has been specifically designed to overcome the methodological limitations of prior studies. The acronym ENVENTOR-iNPH also appears in the manuscript title to reinforce its role as the definitive name of this study protocol.

We hypothesize that ETV will result in cognitive and motor outcomes that are comparable or superior to those achieved with VPS, while minimizing complications and hospitalization duration.

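### The analysis section allows one-tailed tests at an unreduced α of 0.05 for directional hypotheses, names ETV superiority as the example, and leaves unclear whether the primary comparisons are among them

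*Protocol article*

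**What the plan says.** Section 2.11 (Statistical Analysis) gives one significance level: "The threshold for statistical significance will be set at α = 0.05". Two-tailed tests are the default, "unless a specific directional hypothesis is stated (e.g., the anticipated superiority of ETV over VPS), in which case one-tailed tests will be applied". No lower level is given for the one-tailed case. Bonferroni correction is promised where appropriate, without any link to sidedness.

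Later in the same section the power analysis is described as "assuming an effect size of Cohen’s d = 0.5", with "power (1 − β) of 0.80, and α = 0.05 (two-tailed"). The resulting figure is 51 per group. The subsection on primary and secondary endpoints gives 50 per group for the same effect size, power and significance level, without stating sidedness.

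The hypotheses that could trigger the switch differ by outcome:

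- **Primary cognitive and motor outcomes** (section 4, Discussion): "We hypothesize that ETV will result in cognitive and motor outcomes that are comparable or superior to those achieved with VPS".
- **Length of stay** (section 3, Expected Results): ICU and hospital stay are to be compared "with the hypothesis that ETV patients will have shorter stays due to the less invasive nature of the procedure".
- **Complications** (section 3): "Patients in the VPS group are expected to have a higher incidence of device-related complications".

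**The concern.** A one-tailed test at 0.05 asks for half the evidence that a two-tailed test at 0.05 asks for in the favoured direction, and it has no rejection region in the other. Both features matter here. VPS is described in the Abstract as the standard of care, and the Conclusions foresee ETV becoming the preferred operation. An effect against ETV is also plausible on the protocol's own account: section 4.1 describes stoma closure and slower, less predictable cognitive improvement after ETV, and credits VPS with more immediate symptom relief. The usual argument for a one-tailed test, that a difference in the other direction is impossible or of no interest, is therefore not available.

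The trigger is also loose. It depends on whether a directional hypothesis is stated, and the example given is the central comparison of the trial. The formal hypothesis for the primary outcomes is not purely directional. A reader of the article cannot tell which way the primary tests would be run.

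**Working it through.** **Inputs.** From section 2.11: d = 0.5 (so SD = 1 on the standardised scale), α = 0.05, power 0.80. From the endpoints subsection: n = 50 per group, allocated 1:1.

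**1. The plan's own sample size.** The normal approximation is n per group = 2(z_α + z_β)² / d², with z_β = 0.842.

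- Two-tailed, z_α = 1.960: 2 × (2.802)² / 0.25 = 62.8, so 63. The exact noncentral-t calculation gives 64.
- One-tailed, z_α = 1.645: 2 × (2.487)² / 0.25 = 49.5, so 50. The exact calculation gives 51.

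The stated 51 is not reproduced under its two-tailed label. The one-tailed calculation at 0.05 gives both stated figures, 51 (exact) and 50 (normal approximation).

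**2. Power at 50 per group.** The noncentrality is d × √(n/2) = 0.5 × √25 = 2.5.

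| Test at α = 0.05 | Normal approximation | Exact t |
|---|---|---|
| One-tailed | Φ(2.5 − 1.645) = 0.804 | 0.799 |
| Two-tailed | Φ(2.5 − 1.960) = 0.705 | 0.697 |

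With two-tailed testing and 50 per group, the effect detectable with 80% power is d = 0.57.

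**3. False-positive rate for a claim that ETV is better.** A two-tailed test at 0.05 puts 0.025 in the ETV-favouring tail. The one-tailed test puts 0.05 there. The ratio is 2, and 0.05 is the upper tail of a two-sided test at 0.10. With 50 per group (98 degrees of freedom) the standard error of the standardised difference is √(2/50) = 0.20. The observed difference needed to claim ETV better therefore falls from 1.984 × 0.20 = 0.40 SD to 1.661 × 0.20 = 0.33 SD.

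**4. If ETV is truly worse by d = 0.5, with 50 per group.** The two-tailed test declares ETV worse with probability 0.697. The one-tailed test towards ETV has no region in which it can do so. It rejects at all with probability of only about 0.00002, and that rejection would wrongly favour ETV.

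**5. Which outcomes meet the trigger.** Length of stay does, because section 3 calls the direction a hypothesis. Device-related complications carry an expected direction, though these are events that mainly the arm with an implant can have. For the primary outcomes the hypothesis covers equivalence as well as superiority. Section 3 says only that cognitive gains may differ between groups and that gait should improve in both. Against this, the example in section 2.11 speaks of an anticipated superiority of ETV. The passages do not resolve the matter.

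**The case against.** The strongest reply is that two-tailed testing is the default, that the exception needs a stated directional hypothesis, and that a list of the endpoints concerned belongs in a statistical analysis plan that is not shown. Each switched test still has size 0.05, the declared threshold. Much of this stands, and it rules out several stronger readings that a reader might infer:

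- *Most key comparisons become one-tailed.* The documents do not say so. The primary hypothesis is not one of pure superiority, so the status of the primary tests is undetermined.
- *The rule flatly contradicts the power statement.* A two-tailed power analysis agrees with the two-tailed default. The conflict arises only if the example is applied to the powered comparison. The text points that way without saying so.
- *The type I error is doubled outright.* What doubles is the tail favouring ETV, from 0.025 to 0.05, and only for tests that switch.
- *The trial cannot detect harm from ETV.* This holds only for switched tests, and only for formal testing. Section 2.11 also promises effect sizes, so an unfavourable result would be visible.

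The reply does not remove the rule that the article itself fixes: one-tailed testing at an unreduced 0.05, illustrated by the trial's main comparison. Prespecification would justify a one-tailed test only if the endpoints were named, and a level of 0.025 would normally go with it. This text gives neither.

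**Conclusion.** The point holds in this limited form. Section 2.11 permits one-tailed tests at α = 0.05 and does not make clear whether the primary cognitive and motor comparisons are included; on the wording of section 3, length of stay is. For each test that switches, the chance of a false claim for ETV is 5% rather than 2.5%. A true deficit of d = 0.5, which a two-tailed test would find about 70% of the time with 50 per group, could not be formally declared.

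The power figures assume a two-sample t-test with equal variances, 50 analysed per group and no adjustment for multiplicity. The doubling of the favoured tail depends on none of these except the last; a Bonferroni divisor would shrink both tails but leave their ratio at 2.

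The figure of 51 per group labelled two-tailed is a related but separate error. It would remain if the one-tailed clause were deleted, and it should not be counted again here.

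**What to change.** Delete the one-tailed exception from section 2.11. State that all between-group superiority comparisons are two-sided at α = 0.05 and reported with 95% confidence intervals. If a non-inferiority test is planned, as the Conclusions suggest, read it one-sided at 0.025 from the same 95% interval, so that one interval serves both claims. Make the change before any outcome data are analysed by arm.

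The wording change is half a sentence, but it has a consequence for the power claim. Once the one-tailed reading is gone, nothing supports 80% power at d = 0.5 with 50 per group. Section 2.11, the endpoints subsection and the Discussion should then state power of about 70%, or a detectable effect of about d = 0.57 at 80% power. Keeping 80% power at d = 0.5 would need 64 per group, 128 in total before dropout, against the planned 100.
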